
**DISSEMINATION OF RESEARCH FINDINGS**

Research for Equity and Community Health (REACH), the institutional host of the project, links its research to policy and practice through developing close working relationships with policy makers and practitioners and communicating findings using a range of methods to appropriate audiences. The organisation has strong links with community level networks, national as well as international. Nationally, there are links with the National TB control program (NTP), Malaria Control Programme and the HIV Unit of the Ministry of Health. REACH also organises dissemination workshops which pull participants with different expertise but relevant to the project within Malawian. REACH utilises periodic research meetings organised by other research institutions to disseminate findings.

In addition, REACH trust also has links with wider Equi-TB Knowledge program partnership, which has international academic and policy level links. Presentations will be made at international conferences links such as TB Union Conference. Furthermore, to local and international presentations, papers for publication will be submitted to peer-reviewed journals for international audience.

**ORGANISATIONAL FACILITIES**

Research for Equity and Community Health (REACH) Trust is an independent research trust in Malawi which has grown out of a long established collaboration between the Malawi National TB Control Programme, the Department of Sociology, University of Malawi and the Liverpool School for Tropical Medicine.

REACH trust conducts multidisciplinary research to promote equity in health care. It is run by the Director and has a staff compliment of 30 which includes; research managers, senior Researchers, Researchers, Research Assistants and Administration and Finance Staff. The research team includes experts in Sociology, Clinical Sciences and Health Economics.

The trust is well equipped with facilities for research work. Every officer has a computer; either laptop or desk top and are also connected to internet to facilitate literature search and relevant information from websites. It has a saver which is also used for backups

The trust uses different updated software such as Epi-Info, statistical package for social scientist (SPSS), STATA which are mainly used for quantitative data analysis. We also use MAXQDA for qualitative analysis.

**Collaborative agreements:**

The research will be carried out as a true collaborative partnership between research institutions from the south and north. There will be particular emphasis on south-south linkage between REACH of Malawi and Epi-Lab of Sudan.

The project will take a multi-disciplinary approach which builds on the existing strengths and experience of the research partners. The partners in brief are;

- Liverpool School for Tropical Medicine (LSTM) which is the lead organisation and brings technical expertise in disease control, health economics and gender equity.
- Norwegian Heart and Lung Patient Organisation (LHL) brings experience in supporting and promoting patient participation and patient organisations in developing countries, and has supported activities at both REACH and Epi-Lab for many years.
- REACH Trust, Malawi, brings field experience with piloting elements of Triage-Plus and strengths in qualitative social research methods.
- Epidemiological Laboratory (Epi-Lab), Sudan brings epidemiological and survey expertise.

Thus the research organisations will share and apply their skills and experience in a range of disciplines including clinical and public health medicine; systematic research synthesis, health systems development; diagnostics, participatory approaches, gender and equity analysis, survey methods, qualitative research and health economics.

The participatory nature of the involvement of partners at each stage of the action research cycle will lead to improved research capacity among developing country research partners.

**Appendix 1: Health Economy of symptomatic illness modified from[[19]](#endnote-20)**

| **Health related function** | **Unorganised health care economy** | | **Organised health care economy** |
| --- | --- | --- | --- |
| Non marketised | Marketised |
| *Skilled consultations and treatment* | - Use of health related knowledge by household members and respected community members such as primary school teachers - Some specialised services such as traditional midwifery provided outside market | - Traditional healers - Unlicensed and/ or unregulated health workers - Covert private practice by public health staff | - Public Health Preventative services - Licensed health workers and facilities including ANC providers - Licensed/ regulated NGOs |
| *Medical related goods* | - Household/ community production of traditional medicines | - Sellers of traditional and western drugs | - Government pharmacies - Licensed pharmacies |
| *Physical support of acutely ill, chronically ill and disabled* | - Household care of sick and disabled - Community support for AIDS patients, people with disabilities | - Domestic servants - Unlicensed nursing homes | - Government hospitals - Licensed or regulated hospitals and nursing homes |

Access points covered by this project:

**Appendix 2: Informal healthcare providers and their Indicative capacity**

|  |  | | | |
| --- | --- | --- | --- | --- |
| **Elements of Triage-Plus** | Home-Based Care Organisations | Primary Schools | Grocery Stores | Community ANC Clinics |
| 1. **Disease Recognition** | +++ | + | ++ | +++ |
| 1. **Health communication** | ++ | +++ | +++ | + |
| 1. **Diagnostic specimen collection / testing** | ++ | + | + | +++ |
| 1. **Treatment supervision & support** | +++ | + | ++ | +++ |
| 1. **Referral** | ++ | + | ++ | ++ |

**Appendix 3:** Topic guide for assessing capacity of close to community providers

1. *Formation process – whether or not the CTC was formed on initiative from*
   1. Local leaders
   2. NGOs
   3. Government agencies
   4. Religious institutions
   5. Self formation
2. *Affiliation or networks with*
   1. National associations
   2. Religious institutions
   3. NGOs
   4. Government agencies
   5. Health centre
   6. District assembly
   7. Local structures
3. *Funding mechanisms*
   1. District Assembly
   2. International NGOs
   3. Religious organisations
   4. Income generating activities
   5. Contributions
      1. Monetary
      2. In-kind
4. *Demographic information*
   1. Group composition by sex/age
   2. Sex of group leader
   3. Educational qualification of leader

**Appendix 4: SURVEY QUESTIONNAIRE**

| 101 | TB Registration number |  | ___________ | TBREG |
| --- | --- | --- | --- | --- |
| 102 | Type of TB | *Exclude EPTB, relapses and transfer-ins* | 1. New sm+ PTB | TBTYPE |
| 2. New sm- PTB |
| 99. Not Known |
| 103 | Type of DOT |  | 1. Ambulatory | DOTTYPE |
| 2. Guardian-based |
| 3. In-patient |
| 4. Community volunteer |
| 99. Not known |
| 104 | ART Registration number |  |  | ARTREG |
| 105 | Sex |  | 1. Female | SEX |
|  | 2. Male |
| 106 | Age in years? |  | _ _ | AGE |
| 107 | Current marital status? |  | 1. Single never married | MARITAL |
|  | 2. Married |
|  | 3. Divorced/separated |
|  | 4. Widowed |
|  | 99. Not Known |
| 108 | Normal area of Residence. | *Refer to map, exclude if not normally resident in Lilongwe* | _ _ | RESIDE |
|  |  |  |  |  |
| 109 | Total number of household members? |  | _ _ | HOUSETOT |
| 110 | How many of these are children under 12? |  |  | CHILDTOT |
| 111 | Total number of dependants in household. |  | _ _ | DEPEND |

| 201 | When did you first have symptoms? | *Enter month in figures* | | Month _ _ Year _ _ | WHENSICK |  |
| --- | --- | --- | --- | --- | --- | --- |
| 202 | At the very beginning of your sickness, what symptoms did you have for your illness? |  | | 1. Persistent coughing | SYMPSIGN |  |
| 2. Diarrhoea |  |
| 3. Fever/malungo |  |
| 4. Night sweats |  |
| 5. Coughing/spitting blood |  |
| 6. Breathlessness |  |
| 7. Chest pains |  |
| 8. Loss of body weight/kuonda |  |
| 9. Weakness |  |
| 10. Pricking in the chest/zibayo |  |
| 11. Other Specify ------------------------ |  |
|  |  |
| 203 | What did you think you were suffering from? |  | | 1.Cough | SUFFER |  |
| 2.TB |  |
| 3.Chest pains |  |
| 4.Malaria/malungo |  |
| 5.Spirit caused illness-vimbuza |  |
| 6.Bewitchment-kulodza |  |
| 7.Breaking taboos (kaliondeonde/ tsempho/mdulo) |  |
| 8.Asthma/breathlessness (befu) |  |
| 9. Other sp:_____________________________ |  |
| 99. Not known |  |
| 204 | Which major sign prompted you to seek care? | *Circle one* | | 1.Persistent coughing | PROMPT |  |
| 2.Persistent coughing with sputum |  |
| 3.Fever/malungo |  |
| 4.Night sweats |  |
| 5. Coughing/spitting blood |  |
| 6. Breathlessness |  |
| 7.Chest pains |  |
| 8. Loss of body weight/kuonda |  |
| 9. Weakness |  |
| 10. Pricking in the chest/zibayo |  |
| 11. Other body pains |  |
| 12. Other specify__________________ |  |
| 99. Not known |  |
| 205 | What prompted you to get an HIV test | *Circle one* | 1.Persistent coughing | |  | |
| 2.Persistent coughing with sputum | |
| 3.Fever/malungo | |
| 4.Night sweats | |
| 5. Coughing/spitting blood | |
| 6. Breathlessness | |
| 7.Chest pains | |
| 8. Loss of body weight/kuonda | |
| 9. Weakness | |
| 10. Pricking in the chest/zibayo | |
| 11. Other body pains | |
| 12. Other specify__________________ | |
| 99. Not known | |

|  |  |  |  |  | **1st** | **2nd** | **3rd** | **4th** | **5th** | **6th** | **7th** | **8th** | **9th** | **10th** |
| --- | --- | --- | --- | --- | --- | --- | --- | --- | --- | --- | --- | --- | --- | --- |
| 301 | Where did you seek care? | *Go through each stage of the pathway in turn* | 1. Self treat | CARE1 |  |  |  |  |  |  |  |  |  |  |
| 2. Grocery-self treat | CARE2 |  |  |  |  |  |  |  |  |  |  |
| 3. Pharmacy | CARE3 |  |  |  |  |  |  |  |  |  |  |
| 4. Govt facility | CARE4 |  |  |  |  |  |  |  |  |  |  |
| 5. Private clinic | CARE5 |  |  |  |  |  |  |  |  |  |  |
| 6. Traditional healer | CARE6 |  |  |  |  |  |  |  |  |  |  |
| 7. Other (specify) | CARE7 |  |  |  |  |  |  |  |  |  |  |
|  |  |  |  |  |  |  |  |  |  |  |  |
| 99. Not known |  |  |  |  |  |  |  |  |  |  |  |
| 302 | Date the provider was visited? |  |  | DATEVISI |  |  |  |  |  |  |  |  |  |  |
| 303 | Why did you go there? |  | 1. Minor ailment | CAREWHY1 |  |  |  |  |  |  |  |  |  |  |
| 2. Cost low or free treatment |  |  |  |  |  |  |  |  |  |  |  |
| 3. Quick or polite service |  |  |  |  |  |  |  |  |  |  |  |
| 4. Treatment effective for ailment |  |  |  |  |  |  |  |  |  |  |  |
| 5. Close to home/short distance |  |  |  |  |  |  |  |  |  |  |  |
| 6. Referral |  |  |  |  |  |  |  |  |  |  |  |
| 7. Recommended (others or media) |  |  |  |  |  |  |  |  |  |  |  |
| 8. No particular reason |  |  |  |  |  |  |  |  |  |  |  |
| 9. Other sp: ________ |  |  |  |  |  |  |  |  |  |  |  |
| 99. Not known |  |  |  |  |  |  |  |  |  |  |  |
| 304 | Why did you go back more than once?  **Ndi chifukwa chiyani munapitanso?** |  | 1.choose to return when not better  2.Instructed to return if not better  3.Instructed to come for more test  4.No attention/treatment on first visit  5.Was referred  6.Other sp:_______  88.Not applicable  99.Not known | **RETURN** |  |  |  |  |  |  |  |  |  |  |
| 305 | Who decided that you should go there? |  | 1. Self 2. Spouse 3. Household head 4. Relatives/friends 5. Employer 6. Storekeeper referred 7. Referral health worker 8. Othersp:_______   99. Not known | DECIDE |  |  |  |  |  |  |  |  |  |  |
| 306 | a) Did you go there with a guardian? | *If No go to 307* | 1.Yes  2.No |  |  |  |  |  |  |  |  |  |  |  |
|  | b**)** If yes specify the sex of the guardian |  |  | GUARD1 |  |  |  |  |  |  |  |  |  |  |
| 1.Male  2.Female |  |  |
| 307 | How much did you spend (on drugs, fees, consultation)? | *Fill in for each visit to the care provider* | MK | FEES1 | MK | MK | MK | MK | MK | MK | MK | MK | MK | MK |
| 308 | How did you get the money? |  | 1.Own money  2. From Spouse  3.From children/parents  4.From friends/relatives  5.Borrowed (without interest)  6.Borrowed (with interest)  7.Begging  8.Sold assets  9.Othersp:__________ | MONEYHOS |  |  |  |  |  |  |  |  |  |  |

|  |  |  |  |  | 1st | 2nd | 3rd | 4th | 5th | 6th | 7th | 8th | 9th | 10th |
| --- | --- | --- | --- | --- | --- | --- | --- | --- | --- | --- | --- | --- | --- | --- |
| 309 | How did you travel? |  | 1. Did not travel | TPTMODE1 |  |  |  |  |  |  |  |  |  |  |
| 2. Walk | TPTMODE2 |  |  |  |  |  |  |  |  |  |  |
| 3. Bus/Minibus | TPTMODE3 |  |  |  |  |  |  |  |  |  |  |
| 4. Ambulance | TPTMODE4 |  |  |  |  |  |  |  |  |  |  |
| 5 Bicycle | TPTMODE5 |  |  |  |  |  |  |  |  |  |  |
| 6 Own car | TPTMODE6 |  |  |  |  |  |  |  |  |  |  |
| 7 Hired car/Taxi/bicycle | TPTMODE7 |  |  |  |  |  |  |  |  |  |  |
| 8. Stretcher | TPTMODE8 |  |  |  |  |  |  |  |  |  |  |
| 9. Wheel barrow/Oxcart | TPTMODE9 |  |  |  |  |  |  |  |  |  |  |
| 10. Other sp: | TPTMODE10 |  |  |  |  |  |  |  |  |  |  |
| 99. Not Known |  |  |  |  |  |  |  |  |  |  |  |
| 310 | How much did you pay for transport (going there and back including for guardian(s))? | *Fill in for each visit to the care provider*  *(if answer is 2 above then skip this question)* | MK | TPTCOST1 | MK | MK | MK | MK | MK | MK | MK | MK | MK | MK |
| 311 | How much time did you take to go and come back (hrs)? | *Fill in for each visit to the care provider* | Hours | TIME1 | HRS | HRS | HRS | HRS | HRS | HRS | HRS | HRS | HRS | HRS |
| 312 | How much did you spend on food and incidentals? | *Fill in for each visit to the care provider* | MK | FOODFEE1 | MK | MK | MK | MK | MK | MK | MK | MK | MK | MK |

|  |  | | |  | |  | |  | 1st | 2nd | 3rd | 4th | 5th | 6th | 7th | 8th | 9th | 10th | |
| --- | --- | --- | --- | --- | --- | --- | --- | --- | --- | --- | --- | --- | --- | --- | --- | --- | --- | --- | --- |
| 313 | How did you get the money to pay for food, incidentals and transport? | | |  | | 1. Own money | | MONEY1 |  |  |  |  |  |  |  |  |  |  | |
| 2. From spouse (gift) | |  |  |  |  |  |  |  |  |  |  | |
| 3. From children/parents (gift) | |  |  |  |  |  |  |  |  |  |  | |
| 4. From friends/relatives (gift) | |  |  |  |  |  |  |  |  |  |  | |
| 5. Borrowed (without interest) | |  |  |  |  |  |  |  |  |  |  | |
| 6. Borrowed (with interest) | |  |  |  |  |  |  |  |  |  |  | |
| 7. Begging | |  |  |  |  |  |  |  |  |  |  | |
| 8. Sold asset | |  |  |  |  |  |  |  |  |  |  | |
| 9. Other sp: ____________________ | |  |  |  |  |  |  |  |  |  |  | |
| 99. Not known | |  |  |  |  |  |  |  |  |  |  | |
| 314 | Total spent at each care provider? | | | *Calculate sum spent seeking care from each care provider (****for interviewer)*** | | MK | | TOTAL1 | MK | MK | MK | MK | MK | MK | MK | MK | MK | MK | |
|  | |  |  |  |  |  |  |  |  |  |  | |
| 315 | Did you submit sputum? | | | *Fill in for each visit to the care provider* | | 1. Yes | | SPUTUM1 |  |  |  |  |  |  |  |  |  |  | |
| 2. No | |  |  |  |  |  |  |  |  |  |  | |
| 316 | When did you submit sputum? | | | *Enter month in figures* | | Date Month Year | | DATSPU |  |  |  |  |  |  |  |  |  |  | |
| 317 | When did you get results? | | | *Enter month in figures* | | Date Month Year | | DATERES |  |  |  |  |  |  |  |  |  |  | |
| 318 | What was the result of the sputum exam? | | | *Fill in for each visit to the care provider* | | 1. Nothing wrong | | RESULT1 |  |  |  |  |  |  |  |  |  |  | |
| 2. Negative | |  |  |  |  |  |  |  |  |  |  | |
| 3. Positive | |  |  |  |  |  |  |  |  |  |  | |
| 4. No result | |  |  |  |  |  |  |  |  |  |  | |
| 99. Don't know | |  |  |  |  |  |  |  |  |  |  | |
| 319 | | Did you get tested for HIV |  | | 1. Yes 2. No | |  | | | | | | | | | | | |  |
| 320 | | When did you get tested |  | | Day month year | |  | | | | | | | | | | | |  |
| 321 | | What was the result of the test |  | | 1. Positive 2. Negative 3. Don’t know | |  | | | | | | | | | | | |  |

|  |  |  |  |  |
| --- | --- | --- | --- | --- |
| 401 | How many days have you lost work whilst getting a diagnosis for TB? | *Enter days in figures* | _____ | LOSTWORK |
| 402 | How many days have you lost work whilst seeking an HIV test |  |  | LOSTWORK1 |
| 403 | How has TB and care seeking affected your life? |  | 1.Lost job  2.No money to buy food  3. Stigma  4.No money to school fees for children  5. Reduced income  7. Other sp:_______________ | IMPACT |
| 404 | How has the HIV diagnosis affected your life |  | 1.Lost job  2.No money to buy food  3. Stigma  4.No money to school fees for children  5. Reduced income  7. Other sp:_______________ | IMPACT1 |

406a Do you think the services that are being rendered at the clinic are making any difference to the community?

____________________________________________________________________________________________________________________________________________________________

b What do you think about bringing TB diagnostic services into the community?

c. What do you think about bringing HIV testing services to the community?

____________________________________________________________________________________________________________________________________________________________________________________________________________________

| 501 | What is your relationship to head of your household?  **?** | 1. Myself | HHEAD |
| --- | --- | --- | --- |
| 2. Spouse |
| 3. Son/daughter |
| 4. Grandchild |
| 5. Father/Mother |
| 6. Other relation |
| 7. Servant |
| 8. Not related |
| 502 | Sex of head of household | 1. Male | SEXHEAD |
| 2. Female |
| 503 | How much education does he or she have? | 1. Never | HEADEDUC |
| 2. Standard 1 to 5 |
| 3. Standard 6 to 8 |
| 4. JCE |
| 5. MSCE |
| 6. Other sp: _______________ |

| 504 | What is his or her main activity? | 1. Salaried Professional, technical, managerial | | HEADOCC | | |
| --- | --- | --- | --- | --- | --- | --- |
| 1. Salaried – other | |
| 1. Self employed – medium-large business | |
| 1. Self employed – small business | |
| 1. Cash crop farming | |
| 1. Subsistence farming | |
| 1. Casual labour | |
| 1. Contract unskilled labour 2. Unemployed 3. Other (specify) ------------------------ | |
|  | |
| 505 | What was the highest class completed? | 1. Standard 1 to 4 2. Standard 5 to 8 3. JCE 4. MSCE 5. Above MSCE 6. NONE/NEVER ATTENDED SCHOOL | | MAXCLASS | | |
| 506 | What is the main activity you do to earn a living? | 1. Salaried Professional, technical, managerial | | PRIMLIV | | |
| 1. Salaried – other | |
| 1. Self employed – medium-large business | |
| 1. Self employed – small business | |
| 1. Casual labour 2. Contract skilled labour 3. Unemployed 4. Other (specify)----------------- | |
| 507 | When you go for care seeking, who, if anybody, replaces your normal activities? | 1. No one  2. Spouse  3. Male child  4.Female child  5. Male friend/relative/parent  6. Female friend/relative/parent | | REPLACE | | |
| 508 | Do you have a motor vehicle? | 1. Yes | | MOTOR | | |
| 2. No | |
| 509 | What do you use for cooking? | 1. Purchased Firewood 2. Collected firewood 3. Paraffin 4. Charcoal 5. Other specify:_______________ | | FUELSRC | | |
| 510 | Where do you draw water? | | 1. River/stream | | WATERSRC |  |
| 2. Unprotected well | |  |
| 3. Borehole/protected well | |  |
| 4. Public tap | |  |
| 5. Own tap outside house | |  |
| 6. Tap inside the house | |  |
| 7. Other specify: _________ | |  |
| 511 | What is your source of lighting? | | 1. Paraffin | | LITESRC |  |
| 2. Candle | |  |
| 3. Electricity | |  |

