**The novel concept of Triage-Plus** aims to improve disease recognition, health communication, treatment, and referral at the first point of access in the community by working with individuals and structures known to be the first port of call along the health-seeking pathway for the most poor and vulnerable. Triage-Plus augments and builds upon separately documented malaria and TB research experiences with one group of community-based informal care providers in two countries. In the first place store-keepers, also known as “corner shops”, “bottle-stores”, or (in Kenya) “dukas” have been trained to recognise and treat uncomplicated malaria in children and refer those with evidence of complications to the formal public health service in Kenya6,7. Secondly, In South Africa similar group of providers (storekeepers) has provided successful supervision of TB treatment (DOT)[[17]](#endnote-18),[[18]](#endnote-19).

Triage Plus will develop the store keeper experience to improve health care for adults and adolescents by:

1. In addition to storekeepers, incorporate other key informal healthcare providers (antenatal clinics, primary schools and home-based care organisations)
2. Building the links between patients (and their peers and linked volunteers) and informal healthcare providers.
3. Focussing on integrated provision for HIV and TB;

Triage Plus will therefore be an integrated package which can be tailored for use by diverse informal healthcare providers within the formal and informal health sector. As women and girls face the most barriers to access of quality services, Triage Plus will ensure that all its activities are women friendly without being exclusively designed for women. The package will mainstream symptom assessment and recognition practices to enable informal healthcare providers to routinely carry out one or more of the following according to his or her capacity and circumstances and as part of his or her daily activities:-

1. Recognise selected presentations of TB and HIV in adults and adolescents (e.g. chronic cough, weight loss and fevers).
2. Communicate effectively and sympathetically with patients and members of the public to i) encourage and support health seeking behaviour, ii) provide key health messages about TB and HIV (including counselling for HIV testing) and iii) provide reliable information on the services available in the area for these diseases.

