3. Collect appropriate diagnostic specimens (e.g. sputum specimens from chronic cough patients, possibly finger-prick or saliva samples for HIV testing)
4. Recommend and provide appropriate symptom-control treatments (such as anti-pyretics and oral rehydration solutions)
5. Refer to, and receive feedback from, local public health services (e.g. TB patients referred for sputum submission, signposting to voluntary counselling and testing centres for HIV).
6. Store TB and HIV medications distributed by the national programmes and supervise/support TB and or HIV treatment.
7. Be accountable to local patient groups, their peers and associated volunteers.

In this way, Triage-Plus takes the concept of “community mobilisation’ to a new level by empowering different community-based providers to act as more than directors of referral patterns and encourages them to interact, engage with, and augment, formal public health service provision.

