**Intervention package**

The intervention package of the project will encompass several processes aimed at recognising the capacity of the informal healthcare providers, identifying areas of linkage with the district health system and building capacity of both health workers and the informal healthcare providers. Triage-Plus recognises that different informal healthcare providers will not all have the same capacity to deliver all elements of Triage-Plus. The expected pattern of capacities is illustrated in Table 1 but it is clearly recognised that actual capacity will have to be assessed in each setting and may vary according to the setting. A checklist to assess the capacity of the different providers was developed (See appendix 3).

**Table 1:** Matrix for work-packages for informal healthcare providers

| **Element of T+** | **TB** | **HIV** |
| --- | --- | --- |
| **Disease recognition** | 1.Symptom recognition for those presenting to informal healthcare providers  2. identification of chronic coughers in the community | 1. Recognition of HIV syndromes   - Loss of weight - Oral thrush - Shingles - Recurrent diarrhoea |
| **Health communication** | 1.communication within community about TB infection, transmission etc  2. communication with patients regarding stigma  3. health communication re co-infection with HIV | 1.Addressing stigma at community level  2. Safe sex messages  3. Activities with youths  4. Counselling and testing |
| **Diagnostic specimen collection/testing** | 1.community based sputum collection  2. community based sputum transport  3. transport of lab results to patients | 1. Finger-prick HIV testing? 2. Saliva testing? |
| **Treatment supervision and support** | 1. Treatment supervision  2. Group counselling  3. Cotrimoxazole Preventive Treatment  4. Isoniazid Preventive Therapy | 1. psychosocial support pre and post test  2. ARV side-effect support  3. treatment supervision  4. follow-up of ART defaulters |
| **Referral** | 1. identification of chronic coughers  2. Referral for treatment initiation  3. referral for VCT | 1. Referral of syndromic patients for VCT  2. Referral of HIV-positives for treatment initiation  3. Referral of HIV positive cases for Isoniazid Preventive Therapy |

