With a decision to use six large clusters with at least 166,000 population to minimise pollution of the intervention, a proper sample size calculation using simulations will be implemented to guide the analysis plan. The simulation studies will be carried out before the analysis of the study.

*Data collection tools*

Data collection tools for primary and secondary outcome measures

Prior and subsequent to the intervention, the chronic cough registers, TB treatment registers, HTC and ARV Treatment Registers from health facilities in the whole of Lilongwe District (rural and urban) will be audited for patient numbers by health centre catchment area. These data will form the basis for the trial analysis. Place of residence data are crucially important in this study, so that the study staff can locate patients to traditional authorities and health centre catchment areas that are identifiable within either the intervention or the control area. The study staff will, therefore, conduct initial training and continuing quality assurance checks on these registers throughout the study.

Data collection tools for health economic evaluation

A questionnaire survey will be carried out on a random sample of 166 rural new smear positive TB patients (83 at each site) who have registered for treatment (or both) and 200 rural patients who have recently (within last 2 months) registered for ART at the beginning of the intervention and at the end of the trial period. A patient who has both started treatment for smear positive TB and who is registered for ART will count for both samples, therefore the total sample size may be less than 366. These surveys will capture HIV and TB patients’ pathways to care and collect data on individuals’ household assets and on health-seeking experiences around current symptoms, identifying where and why care was sought (appendix 4). Using a cost-effectiveness check-list data will be collected on staff, consumables, transport and other costs incurred by the health service in this intervention.

Data collection for process evaluation

Throughout the duration of the project, detailed monthly reports will be compiled and all minutes will be recorded. All individuals and organisations involved, their roles and their processes of engagement will be documented. Key informant interviews. Semi-structured interviews and in-depth interviews will also be done.

*Data analysis*

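### Survey item 205 asks why the HIV test was taken but offers a single choice from a symptom list, with no specific code for three of the package's four HIV syndromes or for any of its testing routes

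*Protocol*

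**What the plan says.** The Protocol's Data collection process section, under the health economic evaluation, sends the Appendix 4 questionnaire to 166 new smear-positive TB patients and 200 recent ART registrants. This is done at the start of the intervention and again at the end of the trial. Its tasks include recording patients' "health-seeking experiences around current symptoms, identifying where and why care was sought".

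Item 204 asks for the main sign that led the patient to seek care, so a symptom list suits it. Item 205 asks the wider question "What prompted you to get an HIV test" but carries the same list: eleven symptom codes, then "12. Other specify", then a not-known code. One answer is to be circled.

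Table 1 (Intervention package) gives the HIV syndromes that providers learn to recognise: "Loss of weight - Oral thrush - Shingles - Recurrent diarrhoea". The same table includes "Referral of syndromic patients for VCT" and also sends TB patients for testing. The Literature review and justification adds "signposting to voluntary counselling and testing centres for HIV", along with health messages and counselling for testing. Antenatal clinics are one of the provider kinds, and Appendix 2 gives them its top rating for specimen collection and testing.

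**The concern.** Item 205 is the only question on the form that asks why the HIV test was taken. The package is meant to raise ART starts by teaching syndrome recognition and by having community providers counsel and refer people for testing. Item 205 is therefore the natural place to see whether those mechanisms became more common between the two rounds.

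With the present list, a patient who tested because of shingles, or because a home-based care volunteer sent them, has no specific pre-coded answer. If the patient also had a cough or fever, the single-answer rule makes the interviewer choose, and the pre-printed symptom is the easier choice. A real shift towards the package's routes would then show partly as growth in the Other category and partly not at all. At stake is how well the survey answers its own question of why care was sought. The trial's effect estimates are not at stake.

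**Working it through.** No formula applies. The check compares the answer codes with the reasons for testing that the Protocol itself names.

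| Reason for testing | Own code in item 205 | Elsewhere on the form |
|---|---|---|
| Weight loss (Table 1) | Yes: "8. Loss of body weight/kuonda" | Items 202 and 204 |
| Oral thrush (Table 1) | No | Nowhere |
| Shingles (Table 1) | No | Nowhere |
| Recurrent diarrhoea (Table 1) | No | Diarrhoea is code 2 in item 202; absent from item 204 |
| Chronic cough, fever (Literature review) | Yes: codes 1 to 3 | Items 202 and 204 |
| Referral or signposting by a community provider | No | Items 303 (code 6), 304 (code 5) and 305 (codes 6 and 7), per care visit |
| Counselling or health message | No | Partly item 303 (code 7), per care visit |
| Antenatal clinic | No | No specific code |
| TB patient sent for a test | No | Indirectly, from sputum items 315 to 318 and the test date in item 320 |

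Counts for item 205:

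- Specific codes: 11, all symptoms and all the same as in item 204.
- Table 1 HIV syndromes with their own code: 1 of 4, leaving 4 − 1 = 3 without.
- Package testing routes with their own code: 0.
- Residual codes: 2 (12 and 99).

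**What other items recover.** Item 302 dates each care visit and item 320 dates the HIV test, so in some cases a test can be matched to a visit, and items 303 to 305 then show whether that visit followed a referral. The match is incomplete for two reasons. Items 319 to 321 ask whether, when and with what result the patient was tested, but not where or on whose advice. Item 305 names storekeepers and referring health workers but has no code for home-based care groups, patient or NGO groups, or teachers, all of whom the Protocol lists as providers.

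**What write-in text recovers.** Code 12 takes thrush, shingles, diarrhoea or a referral when that is the answer given, and it can be coded afterwards. It recovers nothing when a symptom was circled instead, because no second answer is allowed.

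**The case against.** The strongest reply is that the item has a write-in option and the sample is small. Coding free text from about 200 ART patients per round is routine work, and items 302 to 305 with 320 supply part of the route. This largely stands. A reader might infer that these patients have no answer open to them, or that their reasons cannot be tabulated. The documents do not support that: the answers go into a residual category that needs later coding.

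It can also be said that the list is not purely one of TB symptoms. The Literature review names cough, weight loss and fevers as presentations of TB and HIV that providers are to recognise, and all three have codes. A patient who circles one of them may be giving a true answer that fits the package, so such answers should not be called spurious. What is missing in those cases is the route, not the symptom.

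A reader might also try to size the problem from the ART target: 0.18 × 4,250 = 765 starts against 0.15 × 4,250 = 637.5, a difference of 127.5, and 127.5 / 765 = 16.7%, or about 17 of 100 intervention-arm respondents. This does not follow. It assumes that every extra start has an uncoded reason, but some patients would have cough, fever or weight loss. Others would already be known to be HIV-positive and be referred only for treatment, which says nothing about why they tested. It also assumes that the 200 ART respondents split evenly between arms, which the Protocol does not state.

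Finally, the survey sits under health economics, process questions go mainly to qualitative work, and no analysis stated in the Protocol uses item 205. That limits the importance of the point. It does not explain why an item about the HIV test carries a list written for a different question.

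**Conclusion.** The point holds as a minor improvement to the questionnaire. Item 205 has a specific code for one of the four Table 1 syndromes and for none of the package's testing routes. Its single-answer rule loses the route whenever the patient had both a listed symptom and a referral or counselling and the symptom is circled. Later coding of write-in text cannot restore that, and the visit items restore it only in part.

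The effect is limited to the pathways and health economics survey. The primary outcomes come from the treatment registers and are unaffected. How many respondents would be involved cannot be worked out from the documents. The conclusion rests only on the printed answer lists and on the testing routes the Protocol describes.

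**What to change.** Before the baseline round:

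- Keep all existing symptom codes in item 205. Cough and fever are presentations the package teaches, and TB patients answer the same form.
- Add codes for oral thrush, shingles, recurrent diarrhoea, advice or referral by a community provider (with the kind specified), counselling or a health message, the antenatal clinic, and testing because of TB diagnosis or treatment.
- Replace the single answer with all that apply, followed by one main reason.
- Add oral thrush and shingles to item 202, and oral thrush, shingles and diarrhoea to item 204.
- Use the same list in both rounds.

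The cost is new questionnaire wording, a revised codebook and a slightly longer item. Any interviews already done on the old list would lose exact comparability, which is the reason to make the change before baseline and not between rounds.
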